### Hypothesis

The null hypothesis is that the improvement in cognitive function achieved with EA-CCR is not superior to that achieved with CCR in patients with MCI.

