### Study design

The study design is in accordance with the Standard Protocol Items: Recommendations for Interventional Trials (SPIRIT) and Consolidated Standards of Reporting Trials (CONSORT) 2010 guidelines [24, 25] (see Additional file 1). The study is a prospective, outcome assessor-blinded, parallel-arm, single-center (DongShin University Gwangju Korean Medicine Hospital, Republic of Korea), pilot randomized controlled clinical trial with a 1:1 allocation ratio. A total of 36 participants who meet the inclusion and exclusion criteria will be randomly allocated to an EA-CCR or a CCR (*n* = 18 each) group. Participants in the CCR group will receive RehaCom cognitive rehabilitation only, while those in the EA-CCR group will receive EA at Baihui (GV20), Sishencong (EX-HN1), Fengchi (GB20), and Shenting (GV24) along with RehaCom cognitive rehabilitation. The treatment duration will be 8 weeks in both groups. The primary outcome measure will be an improvement in cognitive function evaluated using the Korean version of the Alzheimer’s Disease Assessment Scale-cognitive subscale (ADAS-K-cog). The secondary outcome measures will include changes in scores for the Korean version of the Montreal Cognitive Assessment (MoCA-K) scale, Center for Epidemiological Studies-Depression Scale (CES-D), Korean Activities of Daily Living (K-ADL) scale, Korean Instrumental Activities of Daily Living (K-IADL) scale, and European Quality of Life Five Dimension Five Level Scale (EQ-5D-5 L). All scale scores will be recorded at baseline (before intervention), 8 weeks after the first intervention (i.e., at the end of the intervention), and 12 weeks after completion of the intervention.

This study protocol complies with the principles of the Declaration of Helsinki and Korean Good Clinical Practice guidelines and has been approved by the Ministry of Food and Drug Safety (Medical Device Clinical Trial Plan approval number 859). The trial has been registered at cris.nih.go.kr (registration number, KCT0003415). The study design is summarized in Figs. 1 and 2.

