### Inclusion criteria

Participants meeting all of the following criteria will be included in the study: (1) age 55 to 85 years; (2) fulfillment of the Petersen diagnostic criteria for MCI [1, 2] with memory impairment for at least 3 months, (3) K-MMSE score of 20–23, (4) MoCA-K scale score of 0–22, (5) Korean language fluency that is adequate for reliable completion of all study assessments, and (6) voluntary provision of informed consent.

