### Sample size estimation

Because of the lack of adequate preliminary studies and limited research funds, study period, and recruitment opportunities, we have adopted a pilot study design with 18 participants in each group.

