### Statistical analysis

A statistician who is not involved in the clinical trial will analyze the final data. We will perform a per-protocol analysis (PP group) for the assessment of efficacy with a supplementary full analysis set (FA group). We will compare the results of analyses between the PP and FA groups and confirm whether there are statistically significant differences between the two groups. If there is a significant difference, the cause will be reviewed and reflected in the efficacy assessment. All statistical analyses will be performed using SPSS version 21 software (IBM Corp.).

Baseline characteristics will be described and compared. Continuous data will be presented as means and standard deviations and compared using the independent *t* test or Wilcoxon rank sum test, while categorical data will be presented as frequencies and percentages and compared using the chi-squared test or Fisher’s exact test.

Changes in scores for the ADAS-K-cog, MoCA-K scale, CES-D, K-ADL scale, K-IADL scale, and EQ-5D-5 L at 8 weeks (at the end of the intervention) and 20 weeks (12 weeks after the end of the intervention), relative to the baseline score, will be analyzed for each group using the paired *t* test or Wilcoxon signed rank test. The degree of changes at each time point will be evaluated using repeated measures analysis of variance and the two-sample *t* test or Wilcoxon rank sum test. Subanalyses will be applied to the statistical analysis according to the participant age. All reported *P* values will be two-sided with confidence intervals at the 95% levels. A *P*value of < 0.05 will be considered statistically significant.

Data for participants who meet the dropout criteria (i.e., < 75% compliance with the protocol procedures [received less than 18 of the 24 scheduled treatment sessions], incidence of SAEs, reluctance to continue the trial, incomplete data that could influence the trial, large error in protocol or significant deviation in implementation, or decision to terminate trial participation by the PI or IRB) will be excluded. Missing values will be implemented by the last observation carried forward method. Interim analyses will not be performed.

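### The arms are compared on unadjusted changes from baseline, which is valid but inefficient, and the added within-arm tests do not address the between-arm hypothesis

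*Protocol article*

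**What the plan says.** The null hypothesis is between-arm: the "improvement in cognitive function achieved with EA-CCR is not superior to that achieved with CCR" (Hypothesis). All six scales are scored before treatment, at its end (week 8) and 12 weeks later (week 20) (Outcome measurements), so each participant should have a baseline score.

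The Statistical analysis section uses that score in three ways.

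- Baseline characteristics are summarised and tested between arms.
- Changes at weeks 8 and 20, "relative to the baseline score, will be analyzed for each group using the paired" t test or the signed rank test, are assessed inside each arm.
- For the comparison of arms, "The degree of changes at each time point will be evaluated using repeated measures analysis of variance" and by a two-sample t test or rank sum test.

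No model with baseline as a covariate appears in the article, and no ANOVA term is named. One threshold applies throughout: a P "value of < 0.05 will be considered statistically significant", and P "values will be two-sided with confidence intervals at the 95% levels". The sample size was set by feasibility: "we have adopted a pilot study design with 18 participants in each group".

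**The concern.** Baseline enters the comparison only by subtraction. That is the best use of it only when the correlation with follow-up is close to 1. Otherwise subtraction adds noise and over-corrects for any chance difference between arms at baseline. With 18 per arm such differences are not rare, and testing them, as planned, does not remove their effect.

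The within-arm tests raise a separate problem. Both arms receive the same 24 RehaCom sessions and repeat the same instruments. MoCA-K is also both an entry criterion ("MoCA-K scale score of 0–22") and a secondary outcome. Both arms may therefore improve even if electroacupuncture adds nothing. A significant change in one arm but not the other says little about the difference between them, yet the section holds these P values to the same 0.05 and does not rank them below the between-arm comparison.

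At stake is the quality of the one estimate that a later trial would use.

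**Working it through.** The plan has no figure to reproduce: 18 per arm is given without an effect size, SD or power.

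**Inputs.** From the article: n = 18 per arm, 1:1 allocation, two-sided 0.05, visits at baseline, week 8 and week 20. Assumed: equal SD of 1 at each visit, correlation rho between baseline and follow-up, and all 36 participants analysed. The per-protocol exclusions may reduce that number.

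**1. Precision.** Per-participant variance is 2(1 − rho) for the change score and 1 − rho² for ANCOVA. The ratio is (1 − rho²)/(2(1 − rho)) = (1 + rho)/2. Estimating the slope multiplies the ANCOVA variance by 1 + 1/(2n − 4) = 1 + 1/32 = 1.03125. The equivalent n is 18 divided by the corrected ratio. Power is from the noncentral t distribution at an assumed true difference of 0.6 SD.

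| rho | change variance | ANCOVA variance | ratio | corrected ratio | 18 per arm is worth | power, change | power, ANCOVA |
|---|---|---|---|---|---|---|---|
| 0.5 | 1.00 | 0.75 | 0.75 | 0.773 | 23.3 | 0.42 | 0.51 |
| 0.7 | 0.60 | 0.51 | 0.85 | 0.877 | 20.5 | 0.62 | 0.67 |
| 0.8 | 0.40 | 0.36 | 0.90 | 0.928 | 19.4 | 0.79 | 0.82 |
| 0.9 | 0.20 | 0.19 | 0.95 | 0.980 | 18.4 | 0.97 | 0.98 |

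**2. Chance imbalance.** The SD of the baseline difference d between arms is √(2/18) = 0.33 SD. It exceeds 0.5 SD in either direction with probability P(|Z| > 0.5/0.333 = 1.5), about 13%. Given d, the change-score contrast is shifted by (1 − rho)d. At rho 0.7 and d = 0.5 that is 0.3 × 0.5 = 0.15 SD, against a standard error of √(0.60 × 2/18) = 0.26 SD. ANCOVA removes this shift.

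**3. Within-arm tests when the arms are equal.** Let both arms improve by the same amount, with rho 0.7, so the change has SD √0.60 = 0.775. Let p be the power of the paired t test with n = 18. Then P(only EA-CCR significant) = p(1 − p), and P(exactly one arm significant) = 2p(1 − p).

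| equal improvement | p | only EA-CCR | exactly one arm |
|---|---|---|---|
| 0.3 SD | 0.34 | 22% | 45% |
| 0.4 SD | 0.54 | 25% | 50% |
| 0.5 SD | 0.73 | 20% | 39% |

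A simulation (5,000 trials per setting, equal 0.4 SD improvement) found exactly one arm significant in 46%, 50% and 41% of trials at rho 0.5, 0.7 and 0.8.

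**4. Validity of the between-arm tests.** In the same simulation with no difference between arms, the change-score t test, ANCOVA, and the ANOVA group and group-by-time terms each rejected in about 4 to 5.5% of trials.

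**5. Repeated measures ANOVA.** If baseline is one of three levels, the group main effect averages the three visits. For a sustained effect δ it estimates (0 + δ + δ)/3 = 2δ/3. With δ = 0.6 SD and rho 0.5, 0.7 and 0.8, its simulated power was 0.30, 0.26 and 0.24. The group-by-time term had 0.44, 0.65 and 0.83.

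**The case against.** The strongest reply is that the plan already contains a valid randomised comparison. That stands. A reader might infer that the planned between-arm tests inflate false positives, or that efficacy will be judged from the within-arm tests. The article supports neither: the between-arm tests keep their level, and nowhere does it say that significance in one arm only will count as efficacy. Regression to the mean and practice effects act on both arms and cancel between them. Selection is on K-MMSE and MoCA-K, not on the primary ADAS-K-cog.

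A reader might also take 39 to 50% as the rate of false claims for EA-CCR. Half of those trials favour CCR alone, so the relevant rate is 20 to 25%. The equal improvement behind it is assumed.

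The precision gain depends on a correlation that the article does not give. It is small at 0.8 and negligible at 0.9, and even at 0.7 power rises only from 0.62 to 0.67. The shift from a 0.5 SD imbalance, 0.15 SD, is smaller than the standard error, and over all randomisations the change-score contrast is unbiased.

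The ANOVA dilution is conditional. It needs baseline as a level and the group main effect read as the treatment effect, and the article states neither. Naming the term can fairly be left to an analysis plan, so its absence is not an error here.

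What remains is that the article does fix the tests, fixes them without the baseline covariate, and places within-arm tests beside the between-arm ones without subordinating them. The pilot label does not answer this: a small trial has the least precision to give away.

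**Conclusion.** The point holds as one of efficiency and interpretation, not of validity. Under assumed correlations of 0.5 to 0.9, baseline adjustment lowers the variance of the between-arm estimate by 25% down to 5% before the small-sample cost; after it, the gain is worth about 5 participants per arm at 0.5 and under half a participant at 0.9. Adjustment also removes the conditional shift of (1 − rho)d from chance imbalance. The within-arm tests cannot support the stated hypothesis, and under the assumptions above they would show EA-CCR alone as significant in about one trial in four or five when the arms do not differ. The ANOVA adds a risk only under the conditional reading described; the group-by-time term is not diluted in this way.

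**What to change.** - Make the between-arm comparison of ADAS-K-cog an ANCOVA of the week-8 score on group and baseline score, in place of the change-score tests and repeated measures ANOVA. Analyse week 20 the same way. Report the adjusted difference with its 95% CI.
- Do the same for the secondary scales, keeping a rank-based check where scores are skewed. K-ADL and K-IADL are candidates, since the Background defines MCI by otherwise normal daily function.
- Present within-arm changes descriptively, without P values.
- Age may be added as a covariate. It does not replace the planned age subanalysis, because a main effect of age says nothing about whether the treatment effect varies with age.

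The cost is one degree of freedom, or two with age, and no new data. It is more than a wording edit: the Quality assurance section requires Ministry and IRB approval of protocol revisions. The article reports that no data had yet been generated, so at that point the change could be made before any result was seen.

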### Outcome measurements

Scores for the ADAS-K-cog, MoCA-K scale, CES-D, K-ADL scale, K-IADL scale, and EQ-5D-5 L will be recorded before treatment, at the end of treatment, and at 12 weeks after treatment completion.

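### Missing scores are filled by LOCF, which fits this three-visit schedule badly, and the plan does not say whether LOCF or the dropout exclusion governs each analysis set

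*Protocol article*

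**What the plan says.** All quotations are from the protocol article.

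- **Visits (Outcome measurements).** Every scale "will be recorded before treatment, at the end of treatment, and at 12 weeks after treatment completion". The Statistical analysis section analyses change at 8 weeks and at "20 weeks (12 weeks after the end of the intervention), relative to the baseline score".
- **Analysis sets (Statistical analysis).** Efficacy is assessed per protocol, with a full analysis set as supplement. The two results are compared, and a significant difference between them is to be reviewed and taken into account in the efficacy assessment.
- **Exclusions (same section).** "Data for participants who meet the dropout criteria" are to be left out. The criteria include low compliance ("received less than 18 of the 24 scheduled treatment sessions"), "reluctance to continue the trial" and "incomplete data that could influence the trial". The sentence names no analysis set.
- **Missing values (next sentence).** "Missing values will be implemented by the last observation carried forward method". No set, outcome or visit is named, and no other method or sensitivity analysis is stated.
- **Course of disease (Background).** MCI is described as a transitional phase in which impairment is progressing.

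**The concern.** There are two linked problems.

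The first is scope. A participant who stops attending may fall under the exclusion rule, the LOCF rule, or one rule in each analysis set. The incomplete-data criterion depends on whether the gap could influence the trial, but no test for that is given and nobody is named to decide it. Whether a gap is dropped or filled is therefore left to judgement, in a trial where participants and practitioners know the allocation. One participant is 1/18 = 5.6% of an arm.

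The second is the method. Before week 8 the only score to carry is baseline, so change is exactly zero at weeks 8 and 20. After week 8 the score carried is the end-of-treatment one. That assumes the effect persists through 12 weeks off treatment, which is what the week-20 visit is meant to test, in a condition the Background calls progressing.

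At stake are the between-group differences at both visits, the precision claimed for them, and the per-protocol versus full-set comparison.

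**Working it through.** The plan has no power, effect-size or dropout figure to reproduce; 18 per group is set by feasibility. Its one derivable number is consistent: 18/24 = 75%.

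**Illustration in SD units of change.** Positive favours EA-CCR. Assumed, not from the documents: no true group difference; both arms gain d8 = 0.4–0.5 SD at week 8 and d20 = 0.1–0.2 SD at week 20; losses are unrelated to outcome, 20% in EA-CCR and 5% in CCR (about 3.6 and 0.9 of 18 people).

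- Losses after week 8, effect at week 20: (0.20 − 0.05) × (d8 − d20) = 0.15 × 0.3 = **+0.045 SD**. Pairing the ranges the other ways (difference 0.2 or 0.4) gives 0.03 or 0.06.
- Losses before week 8, effect at week 8: −0.15 × d8 = **−0.06 to −0.075 SD**.
- Losses before week 8, effect at week 20: −0.15 × d20 = **−0.015 to −0.03 SD**.
- SD of change at week 8 in the arm with p = 0.20 set to zero: √[(1 − p) + p(1 − p)d²]. For d = 0.4 this is √0.8256 = 0.909; for d = 0.5 it is √0.84 = 0.917. The shrinkage is **8–9%**, in that arm only.
- Yardstick: the standard error of a difference with 18 per arm is √(2/18) = 0.333 SD. The shifts of 0.045, 0.06 and 0.075 SD are 14%, 18% and 23% of it. By normal approximation they move a 5% two-sided test to about 5.2–5.6%.

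**Simulation in ADAS-K-cog points.** Negative favours EA-CCR, since a higher score means more deficit. Setup: 18 per arm, 8,000 runs, pooled t test on change at week 20, losses unrelated to outcome. Assumed: SD 6; correlations 0.8 (baseline to week 8), 0.7 (baseline to week 20) and 0.8 (week 8 to week 20). Missing shares are EA-CCR/CCR.

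| Scenario | True difference | LOCF estimate | LOCF SE | Observed-case SE | Rejection, LOCF | Rejection, observed cases |
|---|---|---|---|---|---|---|
| A. Week-8 benefit of 3 gone by week 20; 20%/20% missing at week 20 | 0 | −0.61 | 1.51 | 1.73 | 7.2% | 5.1% |
| B. As A; 30%/10% | 0 | −0.92 | 1.52 | 1.74 | 9.2% | 5.1% |
| C. Both arms gain 3 and lose it; 30%/10% | 0 | −0.58 | 1.54 | 1.74 | 6.8% | 5.2% |
| D. Sustained benefit of 3; 20%/20% lost before week 8 | −3 | −2.39 | 1.43 | 1.73 | 36.4% | 38.1% |
| E. No change in either arm; 20%/20% missing at week 20 | 0 | −0.03 | 1.49 | 1.73 | 5.0% | 5.1% |
| F. Same rise and fall in both arms; 20%/20% missing at week 20 | 0 | 0.01 | 1.54 | 1.73 | 5.1% | 5.0% |

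The estimates match the algebra: A, 0.2 × (−3) = −0.6; B, 0.3 × (−3) = −0.9; C, (0.3 − 0.1) × (−3) = −0.6; D, 0.8 × (−3) = −2.4. LOCF standard errors are 11–17% below those from the scores actually observed. In D, complete data would reject in 46.9% of runs. Most of that power is lost with the data themselves; what LOCF adds is the diluted estimate.

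**The case against.** A reader might infer that the two sentences flatly contradict each other. The text does not support that. Only incomplete data judged able to influence the trial are excluded, and the rules can coexist: exclusions could define the per-protocol set while LOCF fills the full set or minor gaps. A condensed article may also leave that mapping to a fuller document. This part of the objection stands, so the scope is unreconciled rather than contradictory.

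Efficacy also rests on the per-protocol set. There the compliance and withdrawal criteria would remove most early losses, so carried baselines would seldom reach the main result. That stands too. Bias from excluding dropouts is a separate matter. LOCF would still act in the full set, and the plan lets the comparison of the two sets feed into the efficacy assessment.

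Two further strong readings fail. LOCF does not always favour the arm with more losses at week 20: the sign reverses when losses precede week 8, and there is no bias in scenarios E and F. Nor do its standard errors inflate the type I error by themselves. They track the LOCF estimate's own variability (1.51 against an empirical 1.54 in A), and the excess rejections come from bias.

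Finally, this is a 36-person pilot and the illustrated shifts are small. That limits the size of the point but does not make LOCF a suitable method, and LOCF is stated outright rather than left open.

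**Conclusion.** The point holds in a limited form. The plan fixes LOCF as its only missing-data method on a schedule where LOCF either sets change to zero or assumes persistence off treatment. It does not tie the exclusion rule or the LOCF rule to an analysis set.

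Bias arises when scores move between the carried visit and the missing one and that movement, or the amount missing, differs by arm; it can run either way. Separately, counting filled scores as observed claims more precision than the data support.

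Under the assumed 20% versus 5% loss, the shifts run from 0.015 to 0.075 SD in absolute size, at most about a quarter of a standard error. With heavier or more unequal loss, or a lost treatment benefit, the simulated rejection rate reached 6.8–9.2% instead of 5%. Every dropout rate, SD, correlation and trajectory here is assumed, and all losses are taken as unrelated to outcome. The direction and mechanism are secure; the size in this trial is unknown.

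**What to change.** - Replace LOCF with a likelihood-based mixed model for repeated measures: group, visit, group × visit and baseline score, fitted to all observed week-8 and week-20 scores of all randomised participants in the full analysis set. The named software can fit it. A participant with no score after baseline adds no outcome to this model, so report their number by arm.
- State that the dropout criteria define only the per-protocol set, and remove incomplete data from those criteria.
- Keep LOCF at most as a sensitivity analysis.
- Add one sensitivity analysis that assumes worse outcomes for missing EA-CCR values over a range stated in advance.

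Which set should lead the efficacy assessment is a separate question that this change does not settle.

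Cost: analysis wording, somewhat larger standard errors than LOCF would report, and a protocol revision that, under Quality assurance, needs approval from the Ministry of Food and Drug Safety and the IRB. No new data are needed.

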### Confidentiality and data management

All identification records of the participants will be kept confidential. When the results of the study are published, the identification records can be accessed under IRB approval. All documents related to the trial, including CRFs, will be recorded and labeled with participant identification codes and will not reveal the name of the participant. These serial number codes will be stored in sealed, opaque envelopes and kept in a double-locked cabinet. All participant data will be recorded in Excel files by the CRC, and these electronic data will be stored in a password-protected computer. Individuals who are not authorized by the IRB cannot access the data. In addition, raw data (CRFs) will be stored in a cabinet until the end of the study. Written informed consent for the publication of individual details and accompanying images will be obtained from the participants.

## Discussion

The design of this study, including the treatment and evaluation schedules, is based on the designs of several studies evaluating acupuncture treatment for MCI [10, 16].

Although acupuncture has long been used in the treatment of clinical disorders, including cognitive dysfunction, its possible effects on cognitive function have received little attention, resulting in a poor evidence base. This study is expected to provide preliminary evidence for the efficacy, safety, and usefulness of EA for the treatment of MCI.

In this study, cognitive function will be assessed in the initial screening session using the K-MMSE and MoCA-K scale. The Mini-Mental State Examination (MMSE) is one of the most commonly used evaluation tools for cognitive function, while the MoCA scale is a simple and highly sensitive cognitive screening tool [36]. Changes in the ADAS-K-cog score will be recorded as the primary outcome, while changes in scores for the MoCA-K scale, CES-D, K-ADL scale, K-IADL scale, and EQ-5D-5 L will be recorded as secondary outcomes. This will aid in evaluation of the effects of EA-CCR on cognitive function and depression, activities of daily living, and quality of life in patients with MCI.

This protocol has some limitations. First, because of the lack of adequate preliminary studies and the limited research fund, the study has been designed as a single-center pilot study with a small sample size. Second, we will not be able to compare the findings with those for other acupuncture treatment methods for MCI because of the small sample size. Third, although all outcome measures will be measured and recorded by an independent researcher in order to minimize the risk of detection bias, the acupuncturists and participants cannot be blinded to the group allocation.

Nevertheless, the results of this study are expected to provide preliminary evidence regarding the usefulness, safety, and efficacy of EA-CCR for the treatment of MCI, thus providing a foundation for further research.

